## Blinding, unblinding and treatment discontinuation

### Blinding

All participants and investigators will be blinded to the treatment allocation. OUCRU clinical trials unit (CTU) pharmacists will create blinded drug packages (in fully made-up and labelled treatment packs) containing either active drugs or identical placebo sufficient for 6–8 weeks of treatment (dependent on the MRC grade of the participant) according to the prespecified randomisation list, and pre-ship them to the sites. After randomisation, the ward or trial research nurse will take the completed prescription form to the site pharmacy; they will dispense the trial-number specific pack containing the study drug. Unused drug will be returned to the site pharmacy if a participant withdraws from treatment. In ancillary study 3 MRI brain images will be read by an independent neuroradiologist, blind to the treatment allocation and outcomes of the participant.

### Unblinding

If, in the opinion of the local clinician, it is important for good clinical care to unblind treatment the documented request will be discussed with the site Principal Investigator (PI) and Chief Investigator (CI). If it is agreed that knowledge of treatment allocation is essential for the best management of the patient, the unblinding code will be provided by the study pharmacist holding the randomisation list at OUCRU CTU upon documented request from the CI. Generalised clinical deterioration is not sufficient for unblinding, given equipoise about the evidence base supporting the use of dexamethasone regardless of clinical severity. All instances of unblinding will be recorded and reported to the Data Monitoring Committee (DMC) and Trial Steering Committee (TSC).

### Protocol treatment discontinuation

An individual participant may stop study drug early for any of the following reasons: Participant no longer believed to have TBM and all anti-tuberculosis treatment stopped; Confirmatory HIV tests are negative and HIV infection excluded; Unacceptable toxicity or adverse event; Intercurrent illness that prevents further treatment; Any change in the participant’s condition that justifies the discontinuation of treatment in the treating physicians opinion and after discussion with the site PI; Inadequate compliance with the protocol treatment in the judgement of the treating physician; Withdrawal of consent for treatment by the participant.

## Trial management

### Interventions

All participants will receive the standard of care anti-TB drugs and ART drugs according to respective national guidelines. In ART-naive patients, ARTs will be started 6–8 weeks after the start of anti-tuberculosis drugs. Study participants for the main trial will be randomised to receive either dexamethasone or placebo (investigational medicinal product (IMP)) as an extra medication for 6–8 weeks, dependent upon the severity of TBM disease (
Table 2). Dexamethasone/placebo will be dispensed at randomisation from the site pharmacy in intravenous and oral (tablet) formulations. Placebo will be identical in appearance to active drug and dosed and dispensed in the same way. The study drug will be given to participants as early as possible in the treatment of TBM but no later than 7 days from the start of anti-tuberculosis treatment.

**Table 2. T2:** Study drug treatment regimen following randomisation.

	MRC Grade I Daily dexamethasone dose/route	MRC Grades II and III Daily dexamethasone dose/route
Week 1	0.3 mg/kg/24 hrs IV	0.4 mg/kg/24 hrs IV
Week 2	0.2 mg/kg/24 hrs IV	0.3 mg/kg/24 hrs IV
Week 3	0.1 mg/kg/24 hrs IV	0.2 mg/kg/24 hrs IV
Week 4	3mg/24 hrs oral	0.1 mg/kg/24 hrs IV
Week 5	2mg/24 hrs oral	4 mg/24 hrs oral
Week 6	1 mg/24 hrs oral	3 mg/24 hrs oral
Week 7	Stop	2 mg/24 hrs oral
Week 8		1 mg/24 hrs oral

Participants for the DILI strategy study will be randomised to one of three strategies (
Figure 2): Strategies are as follows:

1)Observe: measure transaminases, bilirubin, and INR every 3 days; do not change/stop anti-tuberculosis drugs unless transaminases rise to ≥10x normal, or total bilirubin rises >2.5mg/dl (>43 µmol/L), or INR >1.5 or symptoms of hepatitis worsen (nausea, vomiting, abdominal pain), in which case go to Strategy 3.2)Stop pyrazinamide (Z) alone. Observe, measuring transaminases, bilirubin, and INR every 3 days. If transaminases do not fall to <5x ULN by day 5, or total bilirubin rises >2.5mg/dl (>43 µmol/L), or INR >1.5 or symptoms of hepatitis worsen at any time (nausea, vomiting, abdominal pain), go to Strategy 3.3)Current standard of care (current US CDC guidelines
^4^,
Supplementary File 3).

**Figure 2. f2:**
[figure not shown]
Trial Schema (drug-induced liver injury strategy study).

Patients in the DILI study will undergo regular clinical and blood test monitoring, and there is a clear procedure to follow for moving patients from strategy 1 to strategy 3, or from strategy 2 to strategy 3. We hypothesise that current guidelines for the management of anti-tuberculosis DILI result in the premature interruption of rifampicin and isoniazid (the critical active drugs in early therapy) in those with TBM and are thereby placing participants at risk of poor outcomes. Strategies 1 and 2 may demonstrate improved safety compared to strategy 3. However, regular clinical monitoring, and interim review by an independent data monitoring committee, will be in place to ensure safety of participants in case of any increased adverse events in any of the DILI strategy groups.

DILI related interventions are conducted within the ACT HIV trial, but the DILI strategies (specifically arms 1 and 2, compared with the routine care arm 3) are not expected to increase adverse events. It is in fact anticipated that arm 1 (continue all 4 first line anti-TB drugs) and arm 2 (stop only pyrazinamide) of the DILI study will result in less adverse events due to the continuation of the best and most appropriate anti-TB drugs. Liver function tests will be closely monitored. DILI occurs more frequently in individuals with HIV therefore it is very important that DILI interventions are assessed in an HIV positive group, to avoid unnecessary cessation of first line anti-TB drugs if arms 1 and / or 2 are effective. From a safety perspective, if a patient develops DILI, prior randomisation to dexamethasone or placebo should not affect DILI in an adverse way.

### Anti-tuberculosis treatment

First line anti-tuberculosis treatment will follow current Vietnamese and Indonesian national guidelines. Rifampicin (10mg/kg/24 hrs; maximum 600mg), isoniazid (5mg/kg/24hrs; maximum 300mg), pyrazinamide (25mg/kg/24hrs; maximum 2g) and ethambutol (20mg/kg/24 hrs; maximum 1.2g) will be given for at least the first 2 months of treatment, provided drug resistance is not suspected or proven. Pyrazinamide will then be stopped and rifampicin, isoniazid and ethambutol (at the same doses) will then be given until at least 12 months anti-tuberculosis treatment in total has been given. Patients with visual complications will discontinue ethambutol and an alternative drug will be used in its place. The decision of which fourth drug to use will be made by the treating physician, and is not mandated by the trial. In practice this will be either a fluoroquinolone or streptomycin.

For TBM caused by isoniazid-resistant tuberculosis the attending physician should decide which option to take, dependent upon clinical circumstances. For participants with MDR tuberculosis, second-line treatment should be given as soon as possible, following national guidelines and local policies.

Participants with abnormal liver function tests (LFTs) at screening are eligible to enter the main trial. These patients should be given standard first-line anti-tuberculosis treatment unless blood transaminase concentrations are ≥3 times the ULN with symptoms and signs of hepatitis (vomiting, abdominal pain, jaundice), or ≥5 times the ULN or a rise in serum bilirubin >2.0mg/dL (>34µmol/L) without symptoms. In these participants, initial anti-tuberculosis treatment should consist of levofloxacin, ethambutol, and an aminoglycoside (either kanamycin, amikacin or streptomycin). LFTs should be monitored every 3 days and rifampicin started as soon as blood transaminases are <5x the ULN and/or the symptoms and signs of hepatitis resolve. Once the participant is tolerating a rifampicin-containing regimen isoniazid can be introduced and, if isoniazid is tolerated, the aminoglycoside can be stopped. If pyrazinamide is not used in treatment, at least 12 months of anti-tuberculosis treatment must be given. Participants with liver dysfunction at the start of treatment that require modified initial anti-tuberculosis treatment regimens are ineligible for the DILI strategy study.

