### Drug induced liver injury (DILI)

Hepatitis is the most common drug-induced serious adverse event associated with anti-tuberculosis treatment, occurring in approximately 10% of HIV-uninfected and 20% of HIV-infected patients
^7^. Almost all episodes occur in the first 3 months of anti-tuberculosis therapy, a critical time in TBM treatment. Rifampicin, isoniazid, and pyrazinamide can all cause DILI, although determining which drug is responsible in individual patients can be difficult. Anti-tuberculosis DILI is widely defined as elevation of blood transaminase concentrations ≥3 times the upper limit of normal (ULN) with symptoms, or ≥5 times the ULN without symptoms
^4^. US Centers for Disease Control and Prevention guidelines for pulmonary tuberculosis suggest stopping all anti-tuberculosis drugs in DILI until transaminase concentrations have returned to <2 times the ULN, followed by sequential re-introduction
^4^, however this approach is probably unsafe in those with TBM. We have previously shown that interruptions in first-line anti-tuberculosis chemotherapy for any reason is an independent risk factor for death from TBM
^8^. The suggested concentration thresholds for stopping anti-tuberculosis drugs are not evidence-based. The optimal strategy for managing DILI in TBM is uncertain
^9^. The majority of asymptomatic rises in transaminases (even those >5 times the ULN) will resolve spontaneously, therefore higher thresholds for stopping therapy, perhaps up to 10 times ULN, may be more appropriate. The optimal order and method of drug re-introduction is unknown, and no randomised comparisons have ever been published within the context of TBM treatment.

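### The rifampicin start rule for participants with abnormal entry liver tests does not match the withholding rule in the same paragraph: bilirubin is missing from it, and 'and/or' allows opposite readings

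*Protocol article*

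**What the plan says.** All of the relevant text is in the paragraph on abnormal liver function tests, in the Anti-tuberculosis treatment section of the protocol article.

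- **Withholding rule.** Such participants may enter the main trial and receive standard first-line drugs "unless blood transaminase concentrations are ≥3 times the ULN with symptoms and signs of hepatitis", "or ≥5 times the ULN or a rise in serum bilirubin >2.0mg/dL (>34µmol/L) without symptoms".
- **What they receive instead.** Their "initial anti-tuberculosis treatment should consist of levofloxacin, ethambutol, and an aminoglycoside (either kanamycin, amikacin or streptomycin"), a combination without rifampicin, isoniazid or pyrazinamide.
- **Monitoring.** "LFTs should be monitored every 3 days".
- **Start rule.** The paragraph then has "rifampicin started as soon as blood transaminases are <5x the ULN and/or the symptoms and signs of hepatitis resolve".

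The background section on drug-induced liver injury (DILI) gives the reason for caution about time without first-line drugs: "interruptions in first-line anti-tuberculosis chemotherapy for any reason is an independent risk factor for death from TBM".

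**The concern.** A rule for starting a withheld drug should describe a state different from the one that caused the withholding. Here the two sentences use different criteria. Withholding depends on transaminases, symptoms and bilirubin; starting depends only on transaminases and symptoms. The transaminase limit for starting (<5 times ULN) also lies above the limit for withholding in symptomatic participants (≥3 times ULN). Finally, 'and/or' leaves open whether one start condition is enough or both are needed.

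Two opposite risks follow. Rifampicin may be started with no improvement in the abnormality that led to withholding, or its start may be delayed because no applicable condition can be identified. The protocol treats rifampicin as one of the critical drugs of early therapy, and death is the primary endpoint. The trial runs in four hospitals in two countries, so a rule open to several readings may well be applied differently between them.

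**Working it through.** The plan states no figure on this point, so there is none to reproduce. The check is a logical one.

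**Inputs** (all from the Anti-tuberculosis treatment section):
- Withhold if transaminases are ≥3 times ULN with symptoms; or, without symptoms, if transaminases are ≥5 times ULN or bilirubin is >2.0 mg/dL.
- Start if transaminases are <5 times ULN 'and/or' symptoms resolve.

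**Step 1: entry profiles.** Transaminases (<3, 3 to <5, ≥5 times ULN) × symptoms (yes, no) × bilirubin >2.0 mg/dL (yes, no) gives 3 × 2 × 2 = 12 profiles. The withholding rule covers 8 of them, in four groups of two.

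**Step 2: is the start rule already met at entry?** 'And/or' can be read as 'or' or as 'and'. Separately, a participant who never had symptoms may or may not count as having had them resolve. This gives four literal readings.

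| Withheld group (profiles) | 'Or'; resolving needs earlier symptoms | 'Or'; absence counts as resolved | 'And'; absence counts as resolved | 'And'; resolving needs earlier symptoms |
|---|---|---|---|---|
| Bilirubin only, no symptoms, <5 times ULN (2) | met | met | met | can never be met |
| Symptoms, 3 to <5 times ULN (2) | met | met | not met | not met |
| No symptoms, ≥5 times ULN (2) | not met | met | not met | can never be met |
| Symptoms, ≥5 times ULN (2) | not met | not met | not met | not met |
| **Met at entry, of 8** | **2 + 2 = 4** | **2 + 2 + 2 = 6** | **2** | **0** |

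In the last column, the 4 profiles without symptoms can never meet the rule unless symptoms develop first.

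**Step 3: a fifth, criterion-matched reading.** Suppose 'and/or' means whichever condition corresponds to the reason for withholding. Then <5 times ULN answers the asymptomatic transaminase trigger, resolution of symptoms answers the symptomatic trigger, and both are required when both triggers were present. The three transaminase groups then work. The bilirubin-only group has no corresponding condition.

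**Step 4: what holds under each reading.**
- Bilirubin only: under all five readings the start rule is either met at entry, impossible to meet, or silent.
- Symptoms at 3 to <5 times ULN: met at entry under either 'or' reading; not met under 'and' or under the criterion-matched reading.
- Symptoms at ≥5 times ULN: never met at entry. Under 'or', however, it becomes met if symptoms resolve while transaminases stay ≥5 times ULN, or if transaminases fall to 3 to <5 times ULN while symptoms persist. Both of those states are themselves grounds for withholding.

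**Step 5: size.** The document gives no distribution of participants over these groups. The share of withheld participants who already meet the start rule could therefore lie anywhere from 0% to 100%, and the counts above cannot be turned into numbers of people.

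**The case against.** The strongest reply is the criterion-matched reading. It is natural English, and it makes the rule coherent for every transaminase presentation. That stands, and it limits the defect: on this reading one trigger, bilirubin without symptoms, lacks a start condition. It does not remove the defect, and the text does not say that this reading is intended.

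A second reply is that the paragraph is sequential: the modified regimen comes first, and the start rule is applied at the next three-day liver test. Both sentences can then be carried out in order. But a participant in a conflicting group whose values have not changed would start at that test, so withholding becomes a short delay with no improvement required.

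A third reply is that this is background care, applied alike in both blinded arms. That also stands. A reader might infer a biased dexamethasone comparison, but nothing in the document supports this.

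Other stronger inferences also fail:
- **That most withheld participants are affected.** The counts are of profiles, and the highest (6 of 8) requires symptoms that were never present to count as resolved.
- **That the two rules cannot both be followed.** For some groups and readings they can.
- **That the ambiguity changes eligibility for the DILI strategy study.** That study already excludes on the same liver-test thresholds at day 0, whenever rifampicin is later started.
- **That the cited mortality risk applies directly.** It concerns interruption of first-line drugs; extending it to a delayed start is an analogy.

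**Conclusion.** The point holds in a limited form. The start rule does not match the withholding rule. For participants withheld only for raised bilirubin without symptoms, it fails under every reading considered: it is either satisfied at entry or offers no condition they can meet. For symptomatic participants at 3 to <5 times ULN, it is satisfied at entry if 'and/or' is read as 'or', and not otherwise, so different sites can treat the same presentation in opposite ways.

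The number affected is unknown and may be small. The conclusion rests on the thresholds as printed in the article and on taking the paragraph as a directive to sites. The full protocol is not shown and may word the rule differently. The consequence is for patient safety and consistency between sites, not for the validity of the randomised comparison. The point is worth correcting because a printed safety rule does not work as written and the correction is cheap.

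**What to change.** Reconcile the withholding and start sentences in the Anti-tuberculosis treatment section. Replace 'and/or' with wording that has one meaning. After the change, no participant should meet both rules at once, and each withholding criterion should have a corresponding start condition. A simple test is to run the 8 withheld profiles through the revised text and confirm that each gives one unambiguous answer. The thresholds and the clinical content are for the clinical team to decide; this review takes no position on them.

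The cost is a change of protocol wording and a memo to the sites. No additional tests are needed, because three-day liver function tests are already planned for these participants.

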### Anti-retroviral therapy

ART will be provided for all participants within the current Vietnamese and Indonesian national guidelines. ART in both Ho Chi Minh City and Jakarta is often commenced 6–8 weeks after the start of anti-tuberculosis treatment, with the precise timing left to the discretion of the attending physician. Delays in starting ART of longer than 8 weeks are not encouraged. This practice is supported by our previous trial of immediate versus deferred ART in TBM and consistent with current local practice guidelines
^15^. The optimal time to start ART in TBM is not known, depends upon TBM disease severity and CD4 count, and varies between centres regarding routine practice. Exactly when to start ART is decided upon by the treating physician. A patient with known HIV already on ART will continue this ART when they enter the trial, and during the trial. Whenever possible, patients will be treated with an efavirenz-containing regimen. When viral resistance to first line (NNRTI-based) ART is suspected, case-by-case decisions will be made with regard to HIV-RNA measurement, drug resistance testing, and composition and timing of second line HIV treatment and concurrent tuberculosis treatment, avoiding combined use of rifampicin and protease inhibitors because of strong drug interactions and high risk of toxicity
^16^. Decisions on dose or schedule adjustments for these participants will be made on an individual basis, following the national and local guidelines. If DILI develops ART should not be stopped until all other management has been tried (including interrupting anti-tuberculosis drugs according to the randomised schedule). HIV specialists and liver specialists should be consulted at this point.

### Prophylaxis for opportunistic infections

All participants will receive
*Pneumocystis jirovecii* prophylaxis with co-trimoxazole according to national guidelines (CD4 count <200 cells/mm
^3^). In the DILI strategy study prophylactic co-trimoxazole and/or fluconazole should be stopped before all other drugs if DILI develops.

### Use of concomitant medication

All other concomitant medications essential for participant management are permitted at enrolment, subject to the exclusion criteria of no contraindications to the use of dexamethasone in the judgement of the attending clinician. If use of a concomitant medication that cannot safely be used with dexamethasone becomes essential after randomisation, then the IMP should be stopped and the concomitant medication used without unblinding. Drugs which increase the risk of gastrointestinal bleeding, such as non-steroidal anti-inflammatory drugs (NSAIDS), should be used with caution. Any other oral or intravenously administered corticosteroids are not permitted, unless deemed essential, in which case the study drug should be stopped and replaced by the chosen corticosteroid. The treatment of tuberculosis and HIV once the study drug has been stopped should be determined by national guidelines and the physician responsible for the care of the participant.

### Management of neurological complications occurring after the start of anti-tuberculosis treatment

Neurological deterioration, manifest by falling conscious level or new focal neurological signs, is common after the start of treatment of TBM
^2^. Common causes are hydrocephalus, stroke, tuberculomas, and hyponatraemia, and neurological events occurring within 2 months of starting ART may also be due to IRIS. Whenever possible, all patients with unexplained neurological deterioration should have either brain imaging with computed tomography (CT) or MRI. Corticosteroids are not routinely recommended for the treatment of hydrocephalus or stroke. Tuberculomas may cause significant peri-lesional inflammation and oedema and can manifest as new onset seizures, focal neurological deficit, or globally reduced consciousness. In these circumstances, most physicians recommend using corticosteroids. Therefore, if after clinical and neuroradiological review the attending physician believes a patient’s neurological deterioration is due to tuberculoma(s), open-label dexamethasone is recommended. Study drug should be stopped, if it still being given (without the need for unblinding), and high-dose intravenous dexamethasone (0.4mg/kg/24hrs) should be prescribed. The speed of dexamethasone reduction and the total duration of therapy should be determined on a case-by-case basis by the attending physician.

### Management of IRIS

Untreated HIV-infected patients starting ART treatment for the first time after at least 2 weeks of anti-tuberculosis treatment will be at risk of developing neurological IRIS. A single randomised controlled trial demonstrated that corticosteroids reduced the need for hospitalisation and therapeutic procedures and hastened improvements in symptoms, performance, and quality of life in IRIS associated with non-neurological tuberculosis IRIS
^17^. Therefore, in the absence of other data, if the criteria for IRIS are met, then we recommend the participant should be given open-label dexamethasone or prednisolone. If the participant has IRIS with neurological involvement then intravenous dexamethasone 0.4mg/kg/24 hrs should be given. Oral prednisolone (following the published trial regimen
^17^) should be given for non-neurological IRIS (prednisone 1.5mg/kg per day for 2 weeks, then 0.75mg/kg per day for 2 weeks). IRIS will be diagnosed if the participant meets the antecedent requirements, clinical IRIS criteria, and alternative explanations for the clinical deterioration are excluded if possible (
Supplementary File 2). Cases where alternative diagnoses cannot be fully excluded because of limited diagnostic capacity should be regarded as “probable paradoxical tuberculosis-associated IRIS”. In these probable cases, should resolution of clinical or radiological findings of the suspected IRIS episode occur without a change in tuberculosis treatment or ART having been made, they could then be reclassified as ”paradoxical tuberculosis-associated IRIS” cases.

